#### Depression

Depressive symptoms will be measured using the Patient Health Questionnaire-9 (PHQ-9) [76]. Items capture the severity of symptoms (eg, low interest and fatigue) over the past 2 weeks (eg, “Over the last 2 weeks, how often have you been bothered by... feeling tired or having little energy?”). Responses are rated on a 4-point scale (0 [not at all] to 3 [nearly every day]). Total scores range from 0 to 27, with higher scores indicating greater depressive symptoms (Cronbach α=0.89).

#### Stress

Caregiver stress will be evaluated using the 10-item Kingston Caregiver Stress Scale (KCSS) [79,80]. Items measure care-related stress (eg, “To what extent do you have concerns regarding the future care needs of [care recipient]?”), with ratings on a 5-point Likert scale (1 [no stress] to 5 [extreme stress]). Total scores range from 20 to 50, with higher scores reflecting greater caregiver stress (Cronbach α=0.85).

#### Quality of Life

Subjective quality of life will be assessed using the 5-item Satisfaction With Life Scale (SWLS) [82]. Items ask participants to rate agreement with statements, such as “In most ways, my life is close to my ideal,” on a 7-point scale (1 [strongly disagree] to 7 [strongly agree]). Scores range from 5 to 35, with 20 representing a neutral midpoint and higher scores indicating greater life satisfaction (Cronbach α=0.87).

### Retention and Adherence

A structured, multipronged retention and adherence protocol will be implemented at enrollment to promote engagement, minimize loss to follow-up, and ensure complete data collection. Research staff will be trained to respond sensitively to participant needs, including addressing technical issues, emotional strain, and other barriers to engagement.

To reduce attrition and enhance adherence, participants will receive alternating end-of-week emails from their designated RAs, including check-ins at weeks 1, 3, and 5, and brief check-in surveys at weeks 2 and 4. Engagement will be monitored using CarePair usage analytics (eg, log-in frequency and feature usage), which will guide the content of check-in emails. Participants who have logged in will be contacted to assess their experience, address concerns, and offer optional one-on-one support via Zoom or telephone. Those with little or no engagement will receive reminder emails with encouragement and instructions to participate.

Consistent follow-up will be conducted for participants who do not complete the required study activities (eg, surveys and consent). Weekly reminder emails will be sent in the first 3 weeks of no action, followed by a final phone reminder in the fourth week. Participants who remain unresponsive will be considered lost to follow-up. This structured approach is designed to reinforce expectations, identify participation barriers, and provide personalized support to facilitate continued participation.

Retention will also be supported by incentives. Participants will receive a US $25 Amazon gift card after completing the baseline survey and another US $25 gift card after the 6-week follow-up (after completing all required activities). The fully virtual format further reduces barriers, such as transportation and caregiving responsibilities, making participation more accessible.

Control group activities are designed to match with intervention group activities in terms of interaction frequency and engagement level, minimizing the risk of differential dropout between conditions. All instances of nonadherence or withdrawal, along with reported reasons, will be systematically documented in REDCap to inform feasibility and guide refinements for future trials. While attrition rates of 15% to 30% are common in pilot RCTs and often higher in online interventions [84,85], the study team will monitor retention metrics regularly and, if needed, adjust communication strategies or provide more support to sustain engagement.

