### Control Group

Participants in the attention control group will access a digital folder of articles via Digify, a secure document-sharing platform that allows for controlled access of materials and user-engagement tracking on metrics, including log-ins, articles read, and time spent viewing articles. This folder contains most articles available in CarePair, all focused on ADRD and caregiving topics (3 articles with video components were excluded as these formats are not supported by Digify), but they are not organized by relevance or tailored to caregivers’ needs. Control participants follow the same engagement schedule as participants in the intervention group (ie, 2 log-ins per week for 6 weeks; read 1 article per session). Control activities are designed to match the intervention condition in terms of time commitment and interface interaction, and to ensure consistent engagement across groups while allowing for the isolation of the impact of CarePair’s delivery and personalization features. During onboarding, participants are provided with a deidentified username and password to access the Digify platform, along with step-by-step instructions on the use of the platform.

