### Ethical Considerations

This study was approved by USC’s IRB on September 10, 2025 (protocol#: UP-25‐00690). The study IRB approval letter can be found in Multimedia Appendix 1. The trial is registered on ClinicalTrials.gov (NCT06418971). The trial registration record includes all items from the World Health Organization trial registration dataset (Multimedia Appendix 2), including the primary registry name, trial identifying number, key eligibility criteria, target sample size, primary outcomes, secondary outcomes, funding sources, and sponsor details.

In accordance with the International Council for Harmonisation–Good Clinical Practice E6(R3) guidelines and applicable local regulations, trained IRB-approved research assistants (RAs) will obtain electronic informed consent via REDCap’s e-Consent platform after confirming participant eligibility.

During the virtual consent meeting, RAs will review the study purpose, study procedures, and participant rights (eg, the right to withdraw at any time without penalty) to support participant comprehension, and will encourage questions at any time. They will also explain what participation entails, including time commitments, responsibilities, and potential risks. As consent is an ongoing process, participants will be promptly informed of any protocol changes that could affect their willingness to continue. After the consent meeting, participants will be emailed a copy of the informed consent form signed by both themselves and the consenting RA. See Multimedia Appendix 3 for the informed consent form.

All study personnel are trained in human participants’ protection, confidentiality, and recruitment procedures. Data collection, sharing, and storage will comply with HIPAA and IRB regulations. Each participant will be assigned a unique study identifier, and all data will be stored in a secure, password-protected REDCap database accessible only to IRB-authorized personnel. To maintain confidentiality, all datasets will remain deidentified throughout the study, including during analysis and dissemination.

Participants will receive US $25 for each completed survey and US $20 for an optional interview, for a maximum total of US $70. All payments will be sent as Amazon digital gift cards.

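### Engagement-guided staff contact is specified from CarePair data only, which risks unequal attention between arms; separately, the two payment passages conflict and must be reconciled

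*Protocol article*

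**What the plan says.** **Contact.** Under Retention and Adherence, scheduled contact is general: "participants will receive alternating end-of-week emails from their designated RAs, including check-ins at weeks 1, 3, and 5", with brief surveys at weeks 2 and 4. The engagement-guided layer is narrower: "Engagement will be monitored using CarePair usage analytics (eg, log-in frequency and feature usage), which will guide the content of check-in emails". Two sentences then describe what follows from engagement. The first is "Participants who have logged in will be contacted to assess their experience, address concerns, and offer optional one-on-one support via Zoom or telephone". The second is "Those with little or no engagement will receive reminder emails with encouragement and instructions to participate". A further rule covers incomplete tasks and is not limited by arm: "Consistent follow-up will be conducted for participants who do not complete the required study activities (eg, surveys and consent").

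The Control Group section says Digify provides "user-engagement tracking on metrics, including log-ins, articles read, and time spent viewing articles". The same section says the control is matched on time and interface interaction so that the effect of CarePair's delivery and personalization can be isolated. Retention and Adherence adds that control activities match on how often and how closely participants interact, to limit differential dropout.

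**Payment.** Ethical Considerations states: "Participants will receive US $25 for each completed survey and US $20 for an optional interview, for a maximum total of US $70". Retention and Adherence instead describes a $25 card after the baseline survey and "another US $25 gift card after the 6-week follow-up (after completing all required activities"). Assessments and Outcomes lists four survey time points: baseline, weeks 2 and 4, and week 6.

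**The concern.** An attention control works only if staff attention is delivered by the same rule in both arms. Here the trigger for tailored contact is a data source that exists in one arm. A one-on-one conversation with a research assistant trained to respond to emotional strain could itself move stress, mood or self-efficacy, which are the secondary outcomes. It could also raise log-ins and retention, which are feasibility outcomes. The pilot could not separate these effects from those of the app, and its effect sizes are meant to inform the sample size of the next trial.

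The payment question is different. Two sections state different entitlements. The version that makes the week 6 card conditional weakens the incentive for the survey that carries usability, acceptability and the full secondary scales, among people who have missed something else.

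**Working it through.** **1. Contact rules side by side (Retention and Adherence, Control Group)**

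| Contact | Trigger stated | Limited to one arm as written? |
|---|---|---|
| Check-in emails, weeks 1, 3, 5 | Schedule | No |
| Check-in surveys, weeks 2, 4 | Schedule | No |
| Weekly reminders, then a phone reminder | Required activity not done | No |
| Content of check-in emails | CarePair analytics | Yes |
| Experience check and support offer | Having logged in, under the same engagement monitoring | Yes, if CarePair is the only source |
| Low-engagement reminders | Little or no engagement, same monitoring | Yes, if CarePair is the only source |

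The imbalance is confined to the last three rows. Digify already holds the data needed to run them for controls. The document gives no number of extra contacts and no effect of a contact, so the size cannot be calculated.

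**2. Payment**

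The stated maximum is $70.
- Two paid surveys plus interview: 2 × 25 + 20 = $70. This reproduces the stated figure.
- All four surveys plus interview: 4 × 25 + 20 = $120. This does not.

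The amount therefore fits Retention and Adherence, but the condition still differs. Someone who completes week 6 but missed the week 2 check-in has earned the second card under Ethical Considerations. Under Retention and Adherence that person has not, if the check-in survey is a required activity.

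**3. What the payment condition could do within one arm**

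This applies only if log-ins and articles count as required activities. Assumed values, none from the document: 30% non-adherent; adherers score 0.5 SD better; follow-up is 90% in adherers and 40% to 85% in non-adherers.

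Full-sample mean: 0.5 × 0.70 = 0.350 SD.

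Completer mean = 0.5 × (0.70 × 0.90) / (0.70 × 0.90 + 0.30 × f), where f is follow-up in non-adherers.
- f = 0.40: 0.5 × 0.63 / 0.75 = 0.420, an inflation of 0.07 SD.
- f = 0.85: 0.5 × 0.63 / 0.885 = 0.356, an inflation of about 0.006 SD.

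**4. What it could do to the contrast between arms**

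The payment rule is the same in both arms. If 30% are non-adherent in each, both completer means shift equally and the bias is 0.

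If 20% (intervention) and 40% (control) are non-adherent, with the other assumptions unchanged and f = 0.40:
- True difference: 0.5 × 0.80 − 0.5 × 0.60 = 0.100 SD.
- Completer difference: 0.5 × 0.72 / 0.80 − 0.5 × 0.54 / 0.70 = 0.450 − 0.386 = 0.064 SD.
- Bias: about −0.04 SD, against CarePair. With f = 0.85 it is about −0.002 SD.

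**5. Would reporting retention by arm reveal an imbalance?**

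Take dropout of 15% in one arm and 30% in the other, the ends of the range cited in Retention and Adherence, with 40 per arm.
- Null SE: √(2 × 0.225 × 0.775 / 40) = 0.0934.
- Alternative SE: √((0.15 × 0.85 + 0.30 × 0.70) / 40) = 0.0919.
- Power: Φ((0.15 − 1.96 × 0.0934) / 0.0919) = Φ(−0.36), about 36%.

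**The case against.** The strongest reply is that this reads too much into one condensed sentence. Scheduled emails, check-in surveys and non-completion reminders go to participants generally. CarePair data are said to guide what the emails contain, not whether contact happens. Intervention Fidelity says all communications use scripted templates and refers to a Manual of Operating Procedures, which is not shown and may cover Digify. The pilot is not powered for efficacy, retention is reported by arm, and nonadherence is documented with reasons. On payment, the $70 cap stands in the same sentence, and two paid surveys reproduce it.

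Much of this stands. Most contact is not arm-specific, the text says participants are contacted rather than telephoned, and the $120 is only what a literal reading yields. What does not fall away is that the article states a specific trigger and names one platform. Templates standardize wording, not who receives which message. Reporting retention by arm is a weak safeguard, given about 36% power for a 15% versus 30% difference.

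Three stronger readings are tempting and not supported:
- A reader might infer that the payment rule makes missing data differ by arm. The rule is identical in both arms, so that would need adherence itself to differ, which the document does not state.
- A reader might infer that the rule flatters efficacy. With equal adherence the contrast is unbiased. In the unequal case worked above, the bias is small and runs against CarePair.
- A reader might infer that pay is tied to log-ins. The only examples given of required activities are surveys and consent, so this is open.

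**Conclusion.** The point holds as two separate matters, both worth correcting.

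First, engagement-guided contact is keyed to CarePair analytics alone, which is at odds with the stated purpose of the control. The consequence is a risk of unequal attention, not a demonstrated imbalance. Its size cannot be derived from the document, and it disappears if the operating manual already applies the same rule to Digify.

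Second, the payment passages conflict on which surveys are paid and on what condition, and must be reconciled. Any statistical consequence depends on log-ins or articles counting as required. In that case week 6 usability and acceptability could be inflated by roughly 0.006 to 0.07 SD within an arm under the assumed values, and listwise deletion (Statistical Analysis) would leave it uncorrected. That is modest and bears on the feasibility results rather than on the arm contrast.

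**What to change.** **Contact.** State one engagement trigger, one set of scripts and one support offer for both arms, using Digify metrics for controls. Record the number and type of staff contacts by arm and report them with the feasibility results. If the manual already does this, one sentence in the protocol is enough. The cost is a staff procedure note and some staff time for control contacts. Since 44 participants were enrolled by February 2026, note the date of any change.

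**Payment.** In both sections, state that $25 is paid for each of the baseline and week 6 surveys, $20 for the optional interview, and $70 at most. Pay the week 6 card on completion of that survey, whatever else was missed. Define required activities, and check that the consent form, not seen here, says the same. The cost is a small wording change through the institutional review board, a few extra $25 cards, and a weaker incentive to complete the other activities.

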### Intervention Fidelity

A comprehensive Manual of Operating Procedures has been developed to guide all aspects of training, intervention delivery, and data management. Standardized protocols are in place for participant screening, enrollment, tracking, and communication. All research staff are trained using consistent materials on study procedures, and ongoing team meetings are held to address any issues that may arise with regard to data collection, participant engagement, and CarePair app functionality.

Intervention activities and group assignments will be fixed across participants to ensure consistency. All participants will follow a standardized 6-week study schedule with assessments at predetermined time points. Scripted email templates will be used for all participant communications to maintain uniformity and proactively address potential concerns or barriers to engagement.

To standardize onboarding, intervention participants will receive standardized training materials, including a PDF guide and brief instructional videos on how to use CarePair. The CarePair app’s interface, content, and features will be the same across all intervention participants; however, its organization will be tailored by machine learning algorithms to each participant’s needs and preferences.

### Harms

Given the minimal-risk nature of the study, adverse events (AEs)—defined as any unfavorable or unintended experience associated with participation, whether related to the study or not—are expected to be rare. Potential risks include mild emotional discomfort when responding to survey or interview questions, exposure to ADRD-related content, or minor frustration when navigating digital platforms. There is also a minimal risk of breach of confidentiality. Participants may skip any questions or activities that feel uncomfortable or distressing. Study staff are trained to recognize and respond to participant distress and will provide appropriate referrals, including to the USC Family Caregiver Support Center, for additional support and resources as needed.

All AEs, serious adverse events (SAEs), and unanticipated problems, as well as any protocol deviations, will be documented using designated reporting forms and logs. The principal investigator (PI) will be notified of any AE or SAE within 24 hours, and all required reporting to the USC IRB, designated Safety Officer, and National Institute on Aging (NIA) Program Officer will be conducted in accordance with institutional and federal policies.

### Monitoring

#### Data Monitoring Committee

Given the study’s minimal risk, a formal Data Monitoring Committee is not required for this pilot trial. In line with institutional oversight policies, the study team is required to submit an annual continuing review to serve as a postapproval monitoring report to USC’s IRB, which includes updates on study progress, protocol adherence, and any unanticipated issues and/or AEs. This reporting ensures ongoing compliance with ethical and regulatory standards throughout the study period.

#### Trial Monitoring

No interim analyses or stopping guidelines are planned due to the study’s short duration and minimal risk for participants. The study will follow a structured data and safety monitoring plan. The PI will oversee day-to-day study conduct, data integrity, and participant safety, and the study team will continuously monitor trial progress and data collection to ensure protocol fidelity and protection of human subjects. A designated Safety Officer—independent of the investigative team and study site—will serve in an advisory capacity to the PI and NIA Program Officer. This individual will evaluate the overall progress of the trial, including participant recruitment, data quality, adherence to study procedures, and participant safety.

Safety monitoring reports will be generated every 3 months beginning at the onset of the trial. These reports will summarize aggregate data on participant accrual, retention, demographic characteristics, protocol deviations, and adverse or unanticipated events. Reports will also include analyses of data completeness, timeliness, and overall study progress. The Safety Officer will review safety reports quarterly and provide written feedback and recommendations to the PI and NIA Program Officer regarding the continuation, modification, or termination of the study.

### Statistical Analysis

Descriptive statistics (eg, frequencies, means, and SDs) will be used to characterize the study sample across arms. The intervention’s feasibility and acceptability will be evaluated through recruitment and retention rates, reasons for noncompletion, app usage data (eg, number of log-ins and in-app actions), and participant usability and satisfaction assessments. Independent samples *t* tests for continuous variables and chi-square tests for categorical variables will be used to test for baseline group differences in sociodemographic characteristics and primary and secondary outcome measures (eg, stress and self-efficacy). Relationships among continuous measures will be examined using Pearson correlations. Additional analyses will examine the relationships between covariates (eg, age, education, and kinship), and outcome measures will be examined for inclusion in multivariate models.

To examine preliminary efficacy, within- and between-group differences in secondary outcomes will be assessed. Specifically, we will examine (1) mean values at each time point by group, (2) within-group change from baseline to follow-up, (3) between-group differences in change, and (4) standardized effect sizes (eg, Hedges g) with 95% CIs to guide planning for a future efficacy trial. Missing data will be handled via listwise deletion. A *P *value of .05 will be used to indicate significance in all analyses.

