CarePair needs assessment^e^		—	✓	—	✓
Social support					
Lubben Social Network Scale-6 [69]		—	✓	—	✓
Formal support					
Negative service attitudes and experiences [70]		—	✓	—	✓
Satisfaction with the types and quality of services [71]		—	✓	—	✓
Prior use of services, willingness to use services, and types of services used^e^		—	✓	—	✓
Primary outcomes					
Feasibility					
Recruitment: number/proportion screened, eligible, consented/enrolled, declined, and retained [72]		—	✓	—	✓
Usability: System Usability Scale (SUS) [73,74]; user version of the Mobile Application Rating Scale (uMARS) [75]		—	—	—	✓
Intervention adherence: app usage (measured via number of log-ins); feature usage (measured via number of interactions with resources [eg, saves and notes])		—	—	—	✓
Acceptability					
Satisfaction and acceptability survey^e^		—	—	—	✓
Secondary outcomes					
Depression					
Patient Health Questionnaire-9 [76]		—	✓	—	✓
Patient Health Questionnaire-2 [76,77]		—	—	✓	—
Anxiety					
Generalized Anxiety Disorder-7 [78]		—	✓	—	✓
Generalized Anxiety Disorder-2 [78]		—	—	✓	—
Caregiver stress					
Kingston Caregiver Stress Scale [79,80]		—	✓	—	✓
Self-efficacy					
Revised Scale for Caregiving Self-Efficacy [81]		—	✓	—	✓
Quality of life					
Satisfaction with Life Scale-5 [82]		—	✓	—	✓
Satisfaction with Life Scale-1 [82,83]		—	—	✓	—

a S: screening survey.

b BL: baseline survey.

c FU: 6-week follow-up survey.

d Not applicable.

e Developed for this study.

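### Listwise deletion with a baseline-to-week-6 change leaves collected week 2 and 4 depression, anxiety and life-satisfaction scores out of the effect estimate for anyone who misses week 6

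*Protocol article*

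**What the plan says.** For the secondary outcomes, the Statistical Analysis section of the protocol article lists four summaries: "mean values at each time point by group", change within each group from baseline to follow-up, the between-group difference in that change, and a standardised effect size such as Hedges g with a 95% CI. The effect size is meant for planning the later efficacy trial. Missing data are dealt with by listwise deletion.

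Table 1 (Assessments and Outcomes) schedules two versions of three secondary outcomes:

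| Outcome | Baseline and week 6 | Weeks 2 and 4 |
|---|---|---|
| Depression | "Patient Health Questionnaire-9 [76" | "Patient Health Questionnaire-2 [76,77" |
| Anxiety | "Generalized Anxiety Disorder-7 [78" | "Generalized Anxiety Disorder-2 [78" |
| Quality of life | "Satisfaction with Life Scale-5 [82" | "Satisfaction with Life Scale-1 [82,83" |

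(The bracketed numbers are the article's references.) No version is ticked at all four visits. The Depression, Anxiety and Quality of Life sections describe only the full scales. A footnote to Table 1 defines the follow-up survey as the 6-week one, whereas Study Setting uses the same word for weeks 2, 4 and 6. Stress, self-efficacy and caregiver needs are not measured at weeks 2 and 4.

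**The concern.** The trial collects depression, anxiety and life-satisfaction scores twice between baseline and week 6, but the stated analysis gives them no role beyond a table of means. Combined with listwise deletion, this means that someone who completes the baseline, week-2 and week-4 surveys and then leaves is dropped from the change and from Hedges g as if nothing had been observed after baseline.

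That effect size and its CI are what the pilot is meant to hand on to sample size planning. If those who leave differ from those who stay, and differ in one arm more than in the other, a completers-only estimate can be off in a way that the check-in scores could partly correct.

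A smaller issue sits beside it. The plan for means at each time point does not say which version is tabulated when, and totals from the two versions are not on one scale.

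**Working it through.** **1. What enters the effect estimate.** Change is follow-up minus baseline. On Table 1's definition, follow-up is week 6, so both ends use the same full scale. A missing week-6 score removes the participant, whatever was recorded at weeks 2 and 4. The article gives no power, SD or target effect for these outcomes, so there is no figure of its own to reproduce here.

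**2. Score ranges.** The Depression section says: "Responses are rated on a 4-point scale (0 [not at all] to 3 [nearly every day". The stated full-scale ranges check:
- PHQ-9: 9 × 3 = 27
- GAD-7: 7 × 3 = 21
- SWLS: 5 × 1 = 5 to 5 × 7 = 35

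If the short forms keep the item scale (an assumption), PHQ-2 and GAD-2 run 0 to 2 × 3 = 6, and the 1-item SWLS runs 1 to 7. A caregiver who does not change at all would then have these raw totals at baseline and weeks 2, 4 and 6:
- depression, 1 per item: 9, 2, 2, 9
- anxiety, 1 per item: 7, 2, 2, 7
- life satisfaction, 4 per item: 20, 4, 4, 20

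These cannot be shown as one series. A comparison of arms at any one visit is unaffected, and so is the baseline-to-week-6 change.

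**3. Precision.** Inputs: 40 per arm (Sample Size), and dropout d of 15% and 30% (Retention and Adherence, where these rates are called common in pilot trials). The correlation r between check-in and week-6 scores is assumed to be 0.3 to 0.8, as the article gives none. For g near 0, the half-width is 1.96 × √(2/n), with n = 40(1 − d) completers per arm. If every dropout supplied check-in scores, the variance would be multiplied by 1 − r²d, so the effective n is 40(1 − d)/(1 − r²d). This is an upper bound on the gain.

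| Dropout | Completers per arm | Half-width, completers | Effective n, r = 0.3 to 0.8 | Half-width with check-ins |
|---|---|---|---|---|
| 0% | 40 | 0.44 | 40 | 0.44 |
| 15% | 34 | 0.48 | 34.5 to 37.6 | 0.47 to 0.45 |
| 30% | 28 | 0.52 | 28.8 to 34.7 | 0.52 to 0.47 |

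Worked case, d = 0.30 and r = 0.8: 1 − 0.64 × 0.30 = 0.808; 28/0.808 = 34.7; 1.96 × √(2/34.7) = 0.47.

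**4. Bias, by simulation.** All settings are assumptions: 40 per arm, true standardised effect −0.28, correlation 0.8 between adjacent visits, about 22% missing at week 6, 1,500 trials per pattern. For simplicity the outcome is measured identically at all four visits.

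| Dropout pattern | Completers only | Likelihood, all visits |
|---|---|---|
| Rises with week-4 score, control arm only | −0.14 | −0.27 |
| Rises with week-4 score, both arms alike | −0.26 | −0.28 |
| Random | −0.29 | −0.29 |
| Control arm only, and dropouts skip weeks 2 and 4 | −0.14 | −0.14 |

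A separate run of the first pattern (1,000 trials per setting) varied the adjacent-visit correlation over 0.8, 0.65 and 0.5. Completers only gave −0.16, −0.14 and −0.15; likelihood gave −0.29, −0.27 and −0.26. The bias does not rest on the high correlation.

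A version closer to this trial put short-form scores at weeks 2 and 4 into the model for the full-scale week-6 score (true effect −0.26, correlations again assumed). Completers only gave −0.17 against −0.26 when score-related dropout was confined to the control arm. It gave about −0.26 against −0.27 when both arms dropped out alike. Nothing was recovered when dropouts also missed the check-ins.

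**The case against.** A reader might infer from Table 1 that the short forms distort the efficacy estimate, or that the planned table will show symptoms falling at week 2 and rebounding at week 6. The documents support neither. The change uses one full scale at both ends. The means are by group, so the arms can be compared at each visit. Table 1 lists the versions on separate rows, and nothing says that their totals will be joined. Which version is tabulated when is a clarification, and may be settled in an analysis plan that is not shown.

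A reader might also infer that this trial expects 15% to 30% attrition. The article says that such rates are common in pilot trials, and often exceeded online; it does not adopt them as a design assumption.

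Leaving out the mid-trial scores is not an error in itself: with complete data and an unrestricted model they add nothing to the week-6 contrast. The large simulated bias comes from letting only control dropout depend on the score. The article says that activities are matched across arms to limit differential dropout, and gift cards are tied to the baseline and 6-week surveys, so it is unknown whether people who leave will have done the check-ins. Efficacy is a secondary aim in a pilot that is openly not powered for it.

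Most of this stands and limits the size of the point. What remains is that listwise deletion is a stated choice, not an omission. A better use of data already collected is available, and in none of the patterns examined did it do appreciably worse. Differential dropout also cannot be ruled out in an unblinded trial with two different platforms.

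**Conclusion.** The point holds as a minor, free improvement for three outcomes: depression, anxiety and life satisfaction. As written, check-in scores from people without a week-6 survey contribute nothing to the change or to Hedges g.

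The precision at stake is small: a variance reduction of at most 1% to 10% at 15% dropout and 3% to 19% at 30%, for assumed correlations of 0.3 to 0.8. Bias matters more but is conditional. In the version closest to this trial, the completers-only estimate shrank from −0.26 to −0.17, and only when score-related dropout was confined to one arm. Correcting it requires that dropout be explained by observed scores and that those who leave complete the check-ins.

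The remedy does not reach stress and self-efficacy, two of the four targets in the Secondary Objective, or caregiver needs, because none of these has mid-trial data.

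**What to change.** 1. For depression, anxiety and life satisfaction, replace listwise deletion with a baseline-adjusted likelihood analysis, or multiple imputation, of the full-scale week-6 score. Enter the week 2 and 4 short-form scores as additional outcomes or as auxiliary variables, and keep every participant with any post-baseline score. With a separate mean for each arm and visit and an unstructured covariance, the different score ranges do no harm. Fitting a model to the short-form score alone would not be enough, because the full-scale estimate would stay completers-only.
2. Report means separately for the full forms (baseline, week 6) and the short forms (weeks 2, 4). Alternatively, report the common items at all four visits, if the short-form items sit inside the full scales. The article does not say that they do. It gives the same reference for both anxiety versions but an extra one for PHQ-2 and for the 1-item SWLS; the assumption is least certain for the SWLS item.
3. State in Statistical Analysis that *follow-up* means week 6.

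Cost: analysis code and a few sentences. No new data are needed, and the article plans analysis for August 2026, when data collection is projected to end.
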